### **8.2.3 T cell localization to disease sites**

Localization of transferred antigen-specific CTL to tumor sites will be evaluated in selected patients with surgically accessible disease (disease that is accessible by needle or core biopsy, or that can be excised). Tumor sampling will be performed from 3 to 7 days following the most recent T cell infusion. Single cell suspensions will be prepared and stained to identify antigen-specific CTL by tetramer analysis. Tetramer positive cells will be sorted and analyzed for identity to the original infused CTL clone(s) by PCR of a clone-specific CDR3 region of the T cell receptor. Where possible, these results will be compared with a pre-infusion tumor sample and the peripheral blood. A T cell frequency at least five-fold higher than that found in the peripheral blood or pre-infusion sample will be considered evidence of T cell localization/accumulation in disease sites.

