#### **2.4.6. Use of Interleukin-2 in Adoptive T Cell Therapy**

Analysis of T cell persistence following 22 infusions of CD8+ T cell clones without IL-2 demonstrated a pattern of T cell survival characterized by an average increase in T cell frequency on Day 1, from  $< 1/20,000$  to  $1/480$  PBMCs or  $> 1\%$  of all CD8+ T cells, followed by a steady rapid decline to  $1/1500$  by Day 7 and  $< 1/20,000$  by Day 14. The median survival of CD8+ T cells given without IL-2 was  $6.56 \pm 0.82$  days. To extend the period of in vivo persistence, the study was modified to include four unmodified T cell infusions three weeks apart, the 2nd, 3rd and 4th infusions being accompanied by a 14-day course of low-dose IL-2 following each infusion (at doses of 0.25, 0.50 and 1.0 MU/  $m^2$  s.c. twice daily). These doses are 50- fold less than the high doses of IL-2 administered for the treatment of melanoma, do not mediate the toxicity associated with high-dose infusions, and by itself, has no anti-melanoma effect. Analysis of T cell persistence from 12 infusions of CD8+ T cell clones given with low-dose IL-2 demonstrated a pattern of T cell survival characterized by an increase in frequency to  $1/490$  PBMCs or  $> 1\%$  CD8+ cells in the peripheral blood on Day 1 that was sustained at an average of  $1/890$  PBMCs until Day 14 at which time, IL-2 was discontinued and T cell frequency fell to  $< 1/5700$  by Day 21. The average median survival of CD8+ T cells following an infusion of T cells with IL-2 was  $16.78 \pm 1.6$  days which was significantly longer than that observed in infusions administered to the same patient without IL-2.

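### The five-fold rule in Section 8.2.3 accepts the pre-infusion sample as sole comparator, so it can report tumour localization for cells that are only circulating

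*Protocol*

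**What the plan says.** Protocol Section 8.2.3 plans to look for the infused clone in tumour from selected patients with accessible disease. On timing: "Tumor sampling will be performed from 3 to 7 days following the most recent T cell infusion". On identification: "Tetramer positive cells will be sorted and analyzed for identity to the original infused CTL clone(s) by PCR", using a clone-specific CDR3 region. On comparators: "Where possible, these results will be compared with a pre-infusion tumor sample and the peripheral blood". The decision rule then asks for a frequency in tumour "at least five-fold higher than that found in the peripheral blood or pre-infusion sample" and treats that result as evidence of localization or accumulation at the disease site. The section states no denominator for the frequency and no correction for blood contained in the specimen.

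Section 2.4.6 gives clone frequencies in blood from the completed phase I study. Without IL-2, the clone went on Day 1 "from $< 1/20,000$ to $1/480$ PBMCs", "followed by a steady rapid decline to $1/1500$ by Day 7". With low-dose IL-2 it averaged 1/890 PBMC until Day 14 and fell below 1/5,700 by Day 21. Section 2.6 states that the current design gives a 14-day IL-2 course after both infusions.

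**The concern.** The rule is meant to show that infused cells have gone preferentially to tumour. Only a comparison with blood at the same time tests that. A comparison with the tumour before infusion asks whether the clone is more frequent now than before it was given, and after an intravenous infusion the answer can be yes in any perfused tissue. The CDR3 PCR does not help here: it shows that a cell belongs to the infused clone, not whether it lay in tissue or in blood within the sample.

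Because the two comparators are joined by *or*, the weaker one can decide the case. Adding it can only add positive findings, so the error runs in the favourable direction. It also mixes persistence with homing. The trial asks whether fludarabine keeps cells in blood longer; if it does, higher blood frequencies after Infusion #2 could by themselves produce more samples labelled as localized. The distinction matters to the protocol's own argument: Section 2.1.3 lists poor localization among the likely reasons for limited TIL efficacy, and Section 2.4.3 suggests that lymphopenia may be critical for homing.

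**Working it through.** The protocol states no error rate or expected result for this rule, so there is no figure of its own to reproduce. The check asks what the rule returns when the clone is in the specimen without any accumulation.

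**Inputs**
- Blood before infusion: below 1/20,000 PBMC (Section 2.4.6; reported there for the infusions without IL-2).
- Blood through Day 14 with IL-2: 1/890 PBMC on average (Section 2.4.6). This covers the Day 3 to 7 window and matches the IL-2 regimen of the current design.
- Blood on Day 21 with IL-2: below 1/5,700 (Section 2.4.6).
- Clone frequency in the pre-infusion tumour: not given. Assumed equal to the blood baseline, then varied.
- Share of blood in the biopsy suspension: not given. Varied.

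**1. Rise in blood alone.** (1/890) ÷ (1/20,000) = 20,000/890 = 22.5. The baseline is an upper limit, so the rise is at least 22-fold, against a bar of five.

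**2. Lowest tumour frequency that passes.** Five times 1/20,000 is 1/4,000. Relative to blood this is (1/4,000) ÷ (1/890) = 890/4,000 = 0.22. A tumour in which the clone is at about 22% of its blood frequency passes as localized. Under the blood comparator the same tumour has a ratio of 0.22 and fails.

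**3. Tumour baseline at which blood-level cells stop passing.** A tumour at 1/890 is five-fold above baseline when the baseline is 1/(5 × 890) = 1/4,450. Above that the rule is not met: a baseline of 1/2,000 gives 2,000/890 = 2.2-fold.

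**4. Blood carried over into the specimen.** Let b be the share of blood-derived cells and p0 the tumour baseline. The fold rise is [p0(1 − b) + b/890] ÷ p0 = (1 − b) + b × (1/890)/p0.

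| p0 | b | Fold rise | Five-fold met? |
|---|---|---|---|
| 1/20,000 | 10% | 0.90 + 0.10 × 22.47 = 3.15 | no |
| 1/20,000 | 25% | 0.75 + 0.25 × 22.47 = 6.37 | yes |
| 1/20,000 | 50% | 0.50 + 0.50 × 22.47 = 11.74 | yes |
| 1/100,000 | 5% | 0.95 + 0.05 × 112.36 = 6.57 | yes |

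With p0 = 1/20,000 the crossing point is b = (5 − 1)/(22.47 − 1) = 0.186, or about 19%. If the clone is undetectable before infusion and is scored as zero, any detected cell passes.

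**5. Comparator sample taken before Infusion #2.** If residual clone is below 1/5,700, blood-level cells give a rise of at least 5,700/890 = 6.4-fold. The rule is still met, but with little margin.

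**6. The same null under a blood comparator.** Cells present only as circulating blood give a tumour-to-blood ratio of at most 1, so they cannot reach five-fold, whatever the baseline.

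**The case against.** *The word 'or' may mean above both.* The preceding sentence plans both comparisons, and on that reading the problem disappears. But the text does not say so, the ordinary reading is that either suffices, and the comparisons are made only where possible, which allows a case to be judged on the pre-infusion sample alone. The objection stands as a reason to clarify the sentence.

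*The tumour baseline and the blood share are unknown.* This stands. The 1/20,000 figure is per PBMC in blood, and tumour-reactive cells might already be more frequent in tumour before treatment. A reader might infer that every tumour containing some blood will be declared localized. The documents do not support that: steps 3 and 4 show plausible settings in which the rule is not met.

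*The figures come from another study.* This stands too. The largest available contrast, Day 1 blood without IL-2 (20,000/480 = 41.7-fold), should not be used, because Day 1 lies outside the biopsy window. The Day 7 figure without IL-2 (20,000/1,500 = 13.3-fold) does not match the current regimen. Section 2.4.4 puts lymphocyte counts after fludarabine at 30–40% of baseline or less. That may raise the clone's share of blood cells after Infusion #2, but the protocol gives no figure for it.

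*A strict blood comparison can miss real infiltration.* When the clone is frequent in blood, true accumulation may fall short of five-fold. This is a fair cost of the fix, and it is why cases that meet only the pre-infusion comparison should still be reported.

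*Nothing in the trial's decisions rests on it.* Correct. Localization is not among the objectives in Section 3, it is assessed in selected patients, and no stopping rule, response definition or sample size uses it.

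**Conclusion.** The point holds as a defect in a stated decision rule. Read as written, the pre-infusion comparator cannot distinguish localization from circulation, and the rule can label as localized a tumour that holds less of the clone than blood does. With IL-2 and a tumour baseline equal to the blood baseline, a tumour at about 22% of the blood frequency qualifies, against a background rise in blood of at least 22-fold.

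This rests on three things: the disjunctive reading of *or*, the earlier study's blood frequencies carrying over to this design, and an assumed tumour baseline. For cells at blood level, the false label does not arise if the pre-infusion tumour frequency exceeds about 1/4,450. For blood carry-over with a 1/20,000 baseline, it does not arise at blood shares below about 19%. The supportable statement is that the rule can mislead, not that it always will. A reader might also infer that the trial's main conclusions are at risk; they are not, because safety, persistence in blood and the sample size do not use this rule.

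**What to change.** Replace the rule in Section 8.2.3 with the following: localization means a clone frequency in tumour at least five-fold higher than in peripheral blood drawn at the same time, both expressed on the same denominator (for example per CD8+ cell). The pre-infusion tumour sample, where available, is a supporting comparison. A case that meets only the pre-infusion comparison is reported as *present in tumour*.

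The edit is about one sentence. Appendix D already schedules research blood on Days +3 and +7 after Infusion #1 and on Days +31 and +35, which are three and seven days after Infusion #2. A biopsy between those days would need one research tube on the biopsy day. The price is that fewer samples will qualify, and some true infiltration at times of high blood frequency will be reported only as present.

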## **9. SAFETY ASSESSMENT (RELEVANT DATA BEING OBTAINED)**

Physical exam and Blood Chemistry/Hematology results

Toxicities will be graded according to the Common Toxicity Criteria(66)

## **10. EFFICACY ASSESSMENT (RELEVANT DATA BEING OBTAINED)**

- Radiographic imaging and clinical assessment of residual disease defined previously in post-surgical evaluation. A complete response will be defined as total regression of tumor, a partial response as 50% or more regression of the sum of the perpendicular diameters of all measurable disease, a minor response as less than 50% regression. This assessment will be performed on 4 and 8 weeks after the last infusion and then every 3 months thereafter until disease progression or intervening therapy.

- In vivo persistence of transferred antigen-specific CTL clones as measured by 1) direct assay of PBL for retroviral vector DNA by PCR 2) specific peptide-MHC tetramer staining of peripheral blood lymphocytes followed by flow cytometry analysis, 3) ELISPOT determination of cytokine release following peptide stimulation of peripheral blood lymphocytes and 4) generation of antigen-specific CTL. Isolation of such CTL from patients will demonstrate whether or not transferred CTL will survive and retain their lytic phenotype in vivo. The peak frequency and median survival of T cells following infusions without and with fludarabine conditioning will be determined.

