### 3. OBJECTIVES

#### 3.1 PRIMARY OBJECTIVES

**3.1.1** Assess the safety and toxicity of cellular adoptive immunotherapy in melanoma patients using autologous CD8+ antigen-specific T cell clones following fludarabine conditioning

**3.1.2** Determine the duration of in vivo persistence of adoptively transferred CD8+ antigen-specific CTL clones without and with prior fludarabine-mediated lymphodepletion.

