#### **7.4.5 Treatment with Corticosteroids**

- a. Patients will receive corticosteroids if treatment-related toxicity warranting ablation of T cells is observed
- b. All patients will be hospitalized for the first 48 hours for monitoring. The following dose schedule will be used:

|           |                                    |
|-----------|------------------------------------|
| Day 1     | Intravenous Solu-Medrol at 2 mg/kg |
| Day 2     | Intravenous Solu-Medrol at 2 mg/kg |
| Day 3-4   | Prednisone at 30 mg po b.i.d.      |
| Day 5-6   | Prednisone at 15 mg po b.i.d.      |
| Day 7-8   | Prednisone at 10 mg po b.i.d.      |
| Day 9-10  | Prednisone at 10 mg po q.d.        |
| Day 11-12 | Prednisone at 5 mg po q.d.         |

- c. The in vivo frequency of infused CD4+ T cells will be assayed immediately prior to and 48 hours after the start of steroid therapy. If the frequency of infused CD4+ T cells as determined by peptide-tetramer and RT-PCR analysis of a clone-specific CDR3 region of the TCR at this time has not decrease to 25% or less of the T cell frequency prior to infusion, then, high-dose Solu-Medrol at 2 mg/kg will be given for an additional 48 hours before continuing with the tapering dose schedule.

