### **7.5 CONCOMITANT THERAPY**

- #### **7.5.1**
- Active infections occurring after initiating the study should be treated according to the standard of care.

**7.5.2** The following agents are not allowed while on study: systemic corticosteroids (except as outlined for management of toxicity of non-transduced CTL), immunotherapy (for example, interleukins, interferons, melanoma vaccines, intravenous immunoglobulin, expanded polyclonal TIL or LAK therapy), pentoxifylline, or other investigational agents.

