## **8. SCHEDULE OF EVALUATIONS**

### **Please see Appendix D for Schedule**

#### **8.1 Immunologic Studies.**

Patients receiving T cells will have 40 mls of heparinized blood and a 6ml gray top tube drawn immediately prior to each infusion and 24 hours after each infusion and once weekly for 10 weeks as outlined in appendix D. Samples will be used to evaluate the duration of in vivo persistence, function and trafficking of infused T cell clones. All blood samples will be kept at room temperature and sent to Rm D3-235, FHCRC

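### The first persistence assay in Section 10 looks for a vector the infused clones do not carry, and the steroid-extension rule in 7.4.5(c) names the wrong cell type and the wrong reference time

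*Protocol*

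**What the plan says.** **Persistence.** Primary objective 3.1.2 is to "Determine the duration of in vivo persistence of adoptively transferred CD8+ antigen-specific CTL clones without and with prior fludarabine-mediated lymphodepletion". Section 10 lists four measures of it. The first is "direct assay of PBL for retroviral vector DNA by PCR"; the others are peptide-MHC tetramer staining, ELISPOT, and re-isolation of antigen-specific CTL. Section 7.5.2 allows systemic corticosteroids only "except as outlined for management of toxicity of non-transduced CTL". Appendix A makes the product by peptide-pulsed stimulation, limiting-dilution cloning and anti-CD3/feeder expansion. A clone-identity assay does appear elsewhere: under 8.2.3, tetramer-positive cells from tumor are "analyzed for identity to the original infused CTL clone(s) by PCR of a clone-specific CDR3 region of the T cell receptor". Blood for persistence is already scheduled in 8.1: "Patients receiving T cells will have 40 mls of heparinized blood and a 6ml gray top tube drawn immediately prior to each infusion", with later draws in Appendix D.

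**Steroid extension.** Section 7.4.5(c) says: "The in vivo frequency of infused CD4+ T cells will be assayed immediately prior to and 48 hours after the start of steroid therapy". The trigger for extension is that this frequency, by tetramer and clone-specific PCR, "has not decrease to 25% or less of the T cell frequency prior to infusion". In that case the patient gets two more days of Solu-Medrol at the full 2 mg/kg, and the taper resumes afterwards. Section 6.1 restricts the product to CD8+ clones, and Table 2 of Appendix A makes a CD4-negative, CD8-positive phenotype a release test.

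**The concern.** On persistence, an assay for vector DNA tells us nothing about cells that carry no vector. One of four listed measures of a primary objective is therefore empty, and the molecular assay that would suit these cells is not listed in its place. The three working assays detect antigen specificity, not clone identity, so the patient's own T cells of the same specificity could be counted. The protocol's rationale (2.4.3, 2.5) is that lymphodepletion drives T cell proliferation, so that background need not be the same after the two infusions being compared.

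On steroids, the rule decides whether a patient already being ablated for toxicity gets two more days at 2 mg/kg. Applied literally to CD4+ cells it has no subject, because none are infused. Applied to the CD8+ product, it takes a pre-steroid sample, never uses it, and asks the clone to fall to a quarter of its level before it was given.

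**Working it through.** **Vector PCR.** This part is a comparison of text; no arithmetic applies.

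- Section 10, item 1: the target is retroviral vector DNA.
- Section 7.5.2: the cells are non-transduced.
- Section 6.1 and Appendix A: no vector or transduction step.
- Sections 7.4.5(c) and 8.2.3: the PCR target is the clone's own T cell receptor CDR3 sequence. Section 2.3 reports that PCR and sequencing of receptor genes tracked transferred CMV-specific clones.

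The vector assay has no target in any sample. The CDR3 assay does, but Section 10 omits it.

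**Steroid rule: inputs.** All are PBMC frequencies from the earlier study in 2.4.6, which the calculation assumes carry over to this trial:

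- before infusion: below 1/20,000;
- with IL-2, Day 1: 1/490 (1/480 without IL-2);
- with IL-2, average to Day 14: 1/890;
- with IL-2, Day 21: below 1/5,700, used as the residual level before Infusion #2.

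Ablation is assumed to start within 14 days of an infusion.

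**Formulas.** Target = 0.25 × reference frequency. Required fold fall = frequency at start of steroids ÷ target. Percentage fall = 1 − 1/fold.

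| Reference | Target | Fold fall from 1/490 | Fold fall from 1/890 | Percentage fall |
|---|---|---|---|---|
| Before Infusion #1 (1/20,000) | 1/80,000 | 80,000/490 = 163 | 80,000/890 = 90 | 98.9% to 99.4% |
| Before Infusion #2 (1/5,700) | 1/22,800 | 22,800/490 = 47 | 22,800/890 = 26 | 96.1% to 97.9% |
| Immediately before steroids | 1/1,960 or 1/3,560 | 4 | 4 | 75% |

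The no-IL-2 Day 1 value gives 80,000/480 = 167. Both pre-infusion references are upper bounds, so the first two rows are minimum falls. The Infusion #1 target also lies below the lowest frequency bound reported in 2.4.6.

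**Worked patient.** A 95% fall is 20-fold. It leaves 1/(490 × 20) = 1/9,800 or 1/(890 × 20) = 1/17,800. Both exceed 1/22,800 and 1/80,000, so the extension is triggered in all four combinations. Against the pre-steroid sample, the same patient clears the 25% threshold easily.

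**What still works.** Day 1 over background is at least 20,000/490 = 41-fold, so tetramer staining can measure early persistence.

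**The case against.** The strongest reply is that these are leftover phrases with little consequence. Section 10 does not make the endpoint depend on vector PCR; peak frequency and median survival can come from tetramer counts. The starting background is small: below 1/20,000 against 1/490 is under 2.5% (490/20,000), and a draw before each infusion measures it. CDR3 PCR is not wholly absent for blood, since 7.4.5(c) uses it and 8.2.3 compares with blood where possible. A laboratory following a patient's clone would assay CD8+ cells whatever the text says. The paired draws in 7.4.5(c) suggest that a pre-steroid comparison was meant, and the first two steroid days are intravenous, so the word infusion might refer to them. The fold figures come from a study whose cell dose is not given in 2.4.6. Those for Infusion #2 use a Day 21 residual although Appendix D places that infusion on Day 28 after fludarabine, which also changes the PBMC denominator.

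Much of this stands. The endpoint survives, the size and direction of any bias from endogenous cells cannot be computed from the document, and the fold figures are conditional. The steroid rule reaches only patients already being ablated, and its literal reading errs toward more ablation.

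The defence of the reference time does not stand. The protocol uses infusion as a noun for T cell administration, and the same paragraph speaks of starting steroid therapy when steroids are meant. At best the rule is ambiguous on a dosing decision. That intent can be guessed does not correct an instruction that laboratory and clinic are meant to follow.

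**Conclusion.** The concern holds and should be corrected. Vector PCR gives no information on persistence in any sample, and the clone-specific assay that could take its place is missing from Section 10. The steroid rule is wrong as written on cell type and on reference time. Read for the CD8+ product, it requires at least a 90- to 163-fold fall after Infusion #1 and at least 26- to 47-fold after Infusion #2, where the pre-steroid sample would require 4-fold.

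Those sizes assume that the frequencies in 2.4.6 apply here, that ablation begins within 14 days of an infusion, and that the Day 21 bound represents the level before Infusion #2. The textual contradictions depend on none of these. No effect on sample size, power or the DLT boundaries follows.

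**What to change.** - **Section 10, item 1:** replace the vector assay with PCR for the clone-specific CDR3 sequence of the T cell receptor, run on the blood already drawn under 8.1 and Appendix D.
- **Section 7.4.5(c), cell type:** change CD4+ to CD8+ in both places.
- **Section 7.4.5(c), reference:** set the 25% threshold against the frequency in the sample taken immediately before steroids start.

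The cost is wording in two sections and modest extra laboratory work; no new blood draws are needed. The reference change has one downside: under the assumed frequencies, a patient who just meets the protocol's own 25% threshold goes on to the taper with about 1/1,960 to 1/3,560 infused cells remaining.

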#### **2.4.4. Use of Fludarabine in CLL and in Metastatic Melanoma**

Fludarabine (Fludara, Berlex Inc.) is a purine analog of adenine that inhibits DNA synthesis by impairment of ribonucleotide reductase and DNA polymerase alpha and induces lymphopenia in greater than 30% of patients treated with a standard 5 day course of fludarabine at 25 mg/ m^2 (54). It has significant effects in a wide range of indolent lymphoproliferative diseases including CLL, low grade non-Hodgkin's lymphoma, and Waldenström's macroglobulinemia (55-59), but has no effect on solid tumors, including malignant melanoma (60-62).

Lymphopenia is characterized by a CD4 > CD8 T cell depletion that results in lymphocyte counts falling to 30-40% of baseline or less that is sustained for periods of several weeks to months and is associated with T cell dysfunction-related infections (63, 64). Approximately 25% of patients receiving a 5-day course of treatment will develop an infection that is generally treatable. Patients receiving only a 3-day course of fludarabine exhibit a significantly lower incidence of infection per treatment course (14%) without a significant decrease in anti-lymphoproliferative effect (65).

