## Protocol 1796.00

skewed reconstitution of the immune system is required for anti-tumor effect nor that such a profound level of immunodepletion which was accompanied by serious toxicities, is necessary (or essential), given that a less severe relative lymphopenia can also provide homeostatic proliferative signals to T cells. Fludarabine at 25 mg/m^2 for 3-5 days is known to induce Grade 2-3 lymphopenia (a 30-50% decrease in lymphocyte counts) an effect that is sustained for approximately 4-6 weeks. While some risk associated with lymphopenia is occasionally observed in patients receiving multiple cycles of fludarabine therapy, the degree of immunocompromise is not nearly as severe as the cyclophosphamide/fludarabine conditioning.

This trial will also further delineate the requirements for successful immunotherapy through the adoptive transfer of a uniform population of antigen-specific CD8+ T cell clones so that the reasons for success or failure can be more clearly defined. T cells will first be given in the absence of a conditioning regimen, and then, following a 5 day course of fludarabine. Inpatient analysis of T cell persistence in vivo between the two infusions can be directly compared and the contribution of fludarabine-induced lymphopenia to extending in vivo survival of adoptively transferred T cells evaluated.

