### 4. STUDY DESIGN

This will be a single center, phase I, open-label, nonrandomized study in 12 individuals with metastatic melanoma (Stage IV disease). Antigen-specific T cells targeting one of the A2 or A3-restricted epitopes of the melanoma-associated antigens listed in Table 1 (Appendix A ) will be generated in vitro.

Patients will receive T cell infusions according to the following schedule:

[figure not shown]

Protocol 1796.00

Antigen-specific CD8+ T cell clones will be administered at a dose of  $10^{10}$  cells/m^2 for both Infusions #1 and #2. The median survival of transferred antigen-specific CTL clones in the presence of low-dose IL-2 (250,000 U/m^2) is approximately 17 days. By the end of 21 days, the frequency of transferred CTL is < 0.1% of the total CD8+ population. Fludarabine 25 mg / m^2 will be administered intravenously daily for 5 days prior to the second infusion of antigen-specific CD8+ CTL clones which will also be administered in the presence of low-dose IL-2. Four weeks after the second infusion, patients will be re-evaluated clinically and radiographic to determine the response to therapy. Serial blood draws during this time will allow us to determine if fludarabine lymphodepletion contributed to a prolongation of the median T cell survival beyond the expected 17 days seen with low-dose IL-2 alone.

If serious toxicity related to the T cell infusions is observed following infusion of CTL clones, , a regimen of corticosteroids will be given, and no further T cell infusions will be administered to the patient.

Subjects will be carefully monitored at regular intervals for a total of approximately 9 months following the last infusion. Evaluations after this time will be carried out by the referring physician who will be asked to notify us of the patient's progress. Peripheral blood from the patient will also be drawn. Patients receiving T cells will have up to approximately 4 tablespoons of blood drawn immediately prior to each infusion, 24 hours after each infusion, and then at specified intervals for 4 weeks from the last infusion (Appendix D). Samples will be used to evaluate the duration of in vivo persistence, function and trafficking of infused T cell clones. As a secondary objective, the residual measurable disease in these patients will also be followed to assess the therapeutic efficacy, if any, of these infusions. The estimated time to completion of the study is 24 months.

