## **12. STATISTICAL CONSIDERATIONS**

### **12.1. Sample Size**

The sample size of this clinical trials is modest but sufficiently powerful to fulfill the primary goal of this proposal – determine if prior lymphodepletion extends the survival

Protocol 1796.00

of transferred antigen-specific CD8+ T cell clones. The major immunologic endpoint, in vivo survival of transferred T cells was used to determine patient sample size.

For each patient, the T cell survival of infused CD8+ CTL given alone (Infusion #1) will be compared with subsequent infusion (Infusion #2) given with prior fludarabine conditioning. Since the second infusion given occurs 2 weeks after the first infusion at a time when transferred CD8 cells have disappeared from the circulation, residual cells from the first infusion will not be a confounding factor since, in our previous study, transferred CD8+ T cells were undetectable at two weeks.

Statistical modeling indicates that, with a sample size of 12 patients, and assumed true difference in T cell survival with fludarabine conditioning compared to infusions without of at least 4 days with a standard deviation (SD) of 2 days, we shall have approximately 99% power to detect a statistically significant difference in T cell survival at the two-sided level of significance of .05 (one-sample t-test). These power estimates do not depend on the actual assumed-true values, rather only on the difference between the values. The design of this trial using the first infusion of CD8 T cells administered alone as a baseline for each patient permits intra-patient analysis using paired samples with increased statistical power.

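### Persistence is compared as a frequency, and fludarabine shrinks the denominator before Infusion #2 only, so the peak is inflated and survival can be biased in a direction the protocol leaves open

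*Protocol*

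**What the plan says.** Determining persistence without and with prior fludarabine is a primary objective (Section 3.1.2), and T-cell survival is the variable that sets the sample size (Section 12.1). Section 10 names the quantities compared: "The peak frequency and median survival of T cells following infusions without and with fludarabine conditioning will be determined". The assays are run on peripheral blood lymphocytes and include "specific peptide-MHC tetramer staining of peripheral blood lymphocytes followed by flow cytometry analysis".

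The benchmarks are proportions. Section 4 says of an infusion given with IL-2: "By the end of 21 days, the frequency of transferred CTL is < 0.1% of the total CD8+ population". Section 7.2 gives a similar share of CD8+ cells at 14 days without IL-2. Section 2.4.6 reports earlier results per PBMC: with IL-2, 1/490 on Day 1, an average of 1/890 until Day 14, and below 1/5700 by Day 21.

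On fludarabine, Section 2.4.4 describes "lymphocyte counts falling to 30-40% of baseline or less that is sustained for periods of several weeks to months" and adds that CD4 cells are depleted more than CD8 cells. Section 2.5 gives "a 30-50% decrease in lymphocyte counts) an effect that is sustained for approximately 4-6 weeks". Appendix D places fludarabine on Days 21 to 25 and Infusion #2 on Day 28, with samples to Day 56.

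Section 2.6 credits lymphodepletion, and nothing else, with any survival difference between the two infusions. The protocol nowhere converts a frequency to an absolute count or adjusts for the lymphocyte count.

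**The concern.** A frequency has two parts. The hypothesis concerns the numerator, the transferred cells that remain. Fludarabine acts directly on the denominator, and does so for one infusion of each pair. Pairing within patient does not remove this, because the shift tends the same way in every patient.

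A difference could thus be caused by lymphodepletion, as Section 2.6 says, without any transferred cell living longer: fewer bystander lymphocytes would be enough. At stake is whether the primary immunologic comparison can be read as prolonged persistence.

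**Working it through.** **The plan's own figure.** Section 12.1 plans 12 patients, assumes a true difference of "at least 4 days with a standard deviation (SD) of 2 days", and claims power of about 99% for a two-sided test at 0.05. For a one-sample t-test the noncentrality is 4/(2/√12) = 6.93 on 11 df, and the exact power is 0.99999. If the SD of 2 days applies to each infusion and the two are independent, the SD of the difference is 2√2 = 2.83 and the power is 0.993. The stated figure is reproduced.

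**Effect on the peak.** If a share r of the denominator remains and the transferred-cell count is unchanged, the frequency is multiplied by 1/r.
- Section 2.5, decrease of 30-50%: r = 0.7 to 0.5, so 1.43 to 2.0 times.
- Section 2.4.4, 30-40% of baseline remaining: r = 0.4 to 0.3, so 2.5 to 3.33 times. Its wording allows a deeper fall.

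Both ranges apply total-lymphocyte loss to the whole denominator. If monocytes made up 10-30% of PBMC and did not change (an assumption; the protocol gives no figure), then at r = 0.3 the remaining share would be 0.9 × 0.3 + 0.1 = 0.37 to 0.7 × 0.3 + 0.3 = 0.51, and the inflation 2.7 to 2.0 times. For a CD8+ denominator it is also smaller, since CD4 cells are depleted more. No CD8-specific figure is given.

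**Effect on survival scored at a fixed frequency.** Under exponential decay at rate λ, the crossing time moves by ln(1/r)/λ if r still applies when the threshold is crossed. The Day 14 and Day 21 figures with IL-2 in Section 2.4.6 give λ = ln(5700/890)/7 = 0.265 per day, a half-life of 2.6 days. The last two columns give the chance of a significant paired test with no true effect (n = 12, two-sided 0.05).

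| r | Frequency × | Shift, days | SD 2 | SD 2.83 |
|---|---|---|---|---|
| 0.7 | 1.43 | 1.34 | 0.565 | 0.325 |
| 0.5 | 2.00 | 2.61 | 0.984 | 0.829 |
| 0.4 | 2.50 | 3.45 | >0.99 | 0.970 |
| 0.3 | 3.33 | 4.54 | >0.99 | 0.999 |

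Day 21 is reported only as below 1/5700, so 0.265 is the slowest decay those two points allow and the shifts are upper values for that interval. Other slopes from Section 2.4.6 give, for r from 0.7 to 0.3:
- without IL-2, Days 1-7: ln(1500/480)/6 = 0.190 per day, 1.88 to 6.34 days;
- without IL-2, Days 7-14: ln(20000/1500)/7 = 0.370 per day, 0.96 to 3.25 days;
- with IL-2, Days 1-21: ln(5700/490)/20 = 0.123 per day, 2.91 to 9.81 days.

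**Effect on survival scored against each infusion's own peak.** A constant r cancels and the shift is zero. If the denominator recovers linearly to baseline over 28 to 42 days, then at λ = 0.123 the time to half of peak falls from 5.65 days to 5.04-5.23 (r = 0.7), 4.45-4.77 (r = 0.5) or 3.54-4.01 (r = 0.3). The bias then runs against fludarabine.

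**Timing.** Four weeks from the last fludarabine dose (Day 25) is Day 53, three days before the Day 56 sample. Six weeks is Day 67. The depletion covers most or all of the window.

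**The case against.** The strongest reply is that the powered variable is survival in days, not peak frequency, and that the computation of survival may stand in an analysis plan not at hand. This stands in part. A reader might infer that survival is necessarily overstated after fludarabine. The protocol does not support that, because scoring against each infusion's own peak removes the bias or reverses it. Peak frequency, however, is named in Section 10 and is affected under either definition.

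Second, the ratios in Section 2.4.6 describe an earlier study, and the 0.1% of CD8+ figure describes expected decline; neither is stated as this trial's scoring threshold. That is correct. The fixed-threshold result is therefore conditional, and the error rates in the table are illustrations. They combine an assumed threshold, a slope based on a censored value and the same shift in every patient, while sampling after Day 7 of each infusion is essentially weekly.

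Third, the 2.5 to 3.3-fold end comes from a general account of fludarabine, whereas the rationale for this trial gives the milder 30-50% decrease. Both statements are in the protocol, so both ranges are shown, with the milder one first.

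Fourth, a reader might infer that a positive paired test could never indicate longer survival. That goes too far. Section 2.6 reports medians of 7 and 23 days in the first four patients, treated without IL-2. That 16-day gap exceeds every shift computed here.

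**Conclusion.** The concern holds in a limited form. Peak frequency, a named comparison, is inflated after Infusion #2 with no change in cell number: about 1.4 to 2 times on the Section 2.5 figures and up to 2.5 to 3.3 times on those in Section 2.4.4, less for a CD8+ denominator or one that includes monocytes.

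For survival, the size and direction depend on a definition the protocol does not give. Time to a fixed frequency or detection limit is lengthened, illustratively by 1.3 to 4.5 days (about 1.0 to 9.8 across all slopes in Section 2.4.6), against a planned effect of 4 days. This assumes exponential decay, total-lymphocyte loss in the denominator and depletion persisting at the crossing time. Time relative to each infusion's own peak is unchanged or shortened.

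This is more than detail that an analysis plan could supply: the protocol itself chooses a frequency scale, and the intervention under test acts on that scale. The data are not compromised, since the counts needed for conversion are collected.

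**What to change.** In Sections 10 and 12.1, define peak and persistence as absolute transferred cells per microlitre: the tetramer- or clone-specific fraction of lymphocytes times the same-day absolute lymphocyte count from the CBC differential. A fraction of CD8+ cells must not be multiplied by the lymphocyte count directly. It must first be multiplied by the CD8+ share of lymphocytes from the same flow sample, because Appendix D lists no subset count.

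Define median survival explicitly on that scale, identically for both infusions, and keep frequency as a descriptive secondary. In Section 2.6, limit the attribution statement to differences in absolute counts.

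The cost is small. Appendix D already draws a CBC differential on every research-blood day (0, 1, 3, 7, 14, 21, 28, 29, 31, 35, 42, 49 and 56), so no visit, sample or patient is added. The price is one more calculation per sample and some added measurement error from the CBC count. That error may raise the SD of the paired difference, so the 2-day assumption in Section 12.1 should be reconsidered on the new scale.
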